## Abstract

**Introduction:**

Trauma contributes to the greatest loss of disability-adjusted life-years for adolescents and young adults worldwide. In the context of global abdominal trauma, the trauma laparotomy is the most commonly performed operation. Variation likely exists in how these patients are managed and their subsequent outcomes, yet very little global data on the topic currently exists. The objective of the GOAL-Trauma study is to evaluate both patient and injury factors for those undergoing trauma laparotomy, their clinical management and postoperative outcomes.

**Methods:**

We describe a planned prospective multicentre observational cohort study of patients undergoing trauma laparotomy. We will include patients of all ages who present to hospital with a blunt or penetrating injury and undergo a trauma laparotomy within 5 days of presentation to the treating centre. The study will collect system, patient, process and outcome data, following patients up until 30 days postoperatively (or until discharge or death, whichever is first). Our sample size calculation suggests we will need to recruit 552 patients from approximately 150 recruiting centres.

**Discussion:**

The GOAL-Trauma study will provide a global snapshot of the current management and outcomes for patients undergoing a trauma laparotomy. It will also provide insight into the variation seen in the time delays for receiving care, the disease and patient factors present, and patient outcomes. For current standards of trauma care to be improved worldwide, a greater understanding of the current state of trauma laparotomy care is paramount if appropriate interventions and targets are to be identified and implemented.

STRENGTHS AND LIMITATIONS OF THIS STUDYThe GOAL-Trauma Study will provide a global snapshot of current standards in care for patients undergoing trauma laparotomy, from time of injury to time of discharge.The data set includes aspects of patient and injury factors that will provide improved understanding in the barriers and target areas to improve overall care and outcomes for trauma patients.A global panel of trauma experts has developed with protocol, with significant involvement from patient and public involvement groups.This study is purely observational, therefore, no new treatment or management options are being analysed.

## Introduction

Trauma accounts for approximately 9% of all global deaths^1^ and contributes the greatest loss of disability-adjusted life-years for adolescents and young adults worldwide.^2^ In the context of global abdominal trauma, both blunt and penetrating, the trauma laparotomy is the most commonly performed operation; it can be used both as a means to access identified injuries to organs within the abdomen and pelvis, such as life-threatening bleeding from vessels or solid organs, or contamination from hollow viscus injuries, or for exploratory diagnostic reasons, where cross-sectional imaging may not be easily feasible or available. While mortality rates following a trauma laparotomy are substantial, ranging between 8% and 40%,^3–8^ in recent years the role of damage control resuscitation has transformed trauma care, with significant reduction in mortality and morbidity to trauma patients being observed.^9–11^ However, the standard of care and variation in practice occurring globally for patients undergoing a trauma laparotomy remain relatively unknown.

Comprehensive trauma care is a complex system that includes multiple components, from the first response and prehospital care elements, to definitive facility-based care, and then final rehabilitation and recovery, all while interacting with multiple healthcare services and regional infrastructures.^12^ As such, ensuring optimal trauma care provision can prove difficult, especially where health systems are fragile or under-resourced. A trauma laparotomy is a key procedure within emergency surgical care,^13^ yet if global trauma care is to be improved and optimised, high-quality and nuanced data of patients accessing the trauma system is needed, from across the whole trauma care pathway.

Variation likely exists worldwide in the management and outcomes of patients following trauma laparotomy,^14^ however at present limited data exists. While similar postoperative outcomes have been observed in major trauma centres in a high-income setting,^3^ this is likely not representation on the global scale, alongside varying injury patterns.^15^ Indeed, variations in the epidemiology and management of traumatic brain injury have been noted on the international level.^16^ Ensuring adequate trauma laparotomy care globally is essential if trauma outcomes are to be improved, however a greater understanding of the current state of trauma laparotomy care is paramount if appropriate interventions and targets are to be identified.

The objective of this study is to evaluate both patient and injury factors for those undergoing trauma laparotomy, their clinical management and postoperative outcomes.

## Methods

### Aims

The primary aim of this study is to describe global 30-day postoperative mortality rates for patients undergoing a trauma laparotomy.

The secondary aims of the study are as follows:

To describe the epidemiological characteristics (demographics, injury characteristics, baseline clinical characteristics and surgical casemix) for patients undergoing a trauma laparotomy.To describe the preoperative, perioperative and postoperative processes of care for patients undergoing a trauma laparotomy.

### Study design

We will conduct a prospective multicentre observational cohort study of patients undergoing a trauma laparotomy. We will recruit centres through pre-existing research networks, using a snowballing technique to expand registration of centres. We will enrol eligible patients undergoing emergency trauma laparotomy over a consecutive 30-day period at individual centres during the study dates, with patients followed until discharge, death or 30 days postoperatively, whichever comes first. All data will be submitted to a central study team by 30 days after the end of their respective data study period.

Any hospital worldwide that performs emergency trauma surgery will be eligible to participate, including both trauma centres and trauma units; a minimum of one case must be submitted by the centre during the 30-day study period to be eligible. Each centre’s team will be composed of a local study lead, with maximum three members of the local study team for each data collection period. Independent data validators will also be required for select centres. The data collection periods will run between 1 April 2024 and 31 December 2024, with final 30-day follow-up for the final patients expected to be completed on 30 January 2025.

The study will be overseen and managed by the study’s steering committee, with external advice provided by the study’s advisory committee (see online supplemental material), all involved in the study design and protocol write-up.

10.1136/bmjopen-2023-083135.supp1Supplementary data

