### Data collection

We aim to collect system, patient, process and outcome data. A data set will be collected on all patients undergoing a trauma laparotomy within the inclusion period (see online supplemental table 1). The included data fields were based on work by similar studies and refined through iterative consultation with a global interdisciplinary consortium of clinicians involved in trauma care.

Data will be collected through access to patient records only at each centre, performed by members of the local study team. The patient will not be contacted directly in any capacity during their inpatient stay or after the study and no direct involvement in patient care will occur. Data will be collected directly onto a well-established secure web-based system, REDCap cloud (or recorded temporarily onto a hard copy data collection form and uploaded to REDCap at a later date).

A local data validator (independent of the local study team) will be appointed at select participating centres to assess the data accuracy and ascertainment. They will independently assess case ascertainment and collect data on two variables, namely the date and nature of the operation. Each centre’s local lead will also be asked to complete a centre survey, to provide more background on their specific hospital settings, infrastructure and capacity. A pilot study was run prior to the main data collection period at multiple centres globally to ensure feasibility in the methodology across multiple settings.

The data collected will include a pragmatic set of variables that allow the proposed research to be conducted, but minimise both risk of identification and exclude extraneous possibly sensitive medical information. Local requisite ethics and approvals will be applied for and be in place before any data collection occurs. The patient consent procedure will depend on the local and national guidance for the collaborating hospitals; specific guidance will be provided to collaborators on consenting if necessary and, where required, written consent forms will be obtained for patient inclusion in the study.

Access to the main data for analysis will be limited to named researchers from the steering committee, however, collaborators at each centre will be able to access their own institutions data during the study period.

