### Statistical analysis

A formal statistical analysis plan will be produced. However, in brief, participating centres will be stratified based on their country into groups based on their Human Development Index (HDI) rank, with 30-day mortality then reported for each HDI group. Further analyses will include stratification against other economic and health indices, and multivariable logistic modelling will be used to investigate primary and secondary study aims.

As there are a lack of data on trauma laparotomy globally, performing an accurate sample size calculation is not feasible. Data suggest that 30-day mortality rates following trauma laparotomy in high-income countries (HICs) are around 9%^3^ and in low-income and miffle-income countries (LMICs) are around 17%^17–19^; using an alpha value=0.05 and power=80%, to show a difference between HIC and LMIC settings, a total of 552 patients are required to be recruited to the study. Based on data from other observational studies,^3 7 8^ we would expect over a 30-day observation period each centre to commit around 3–5 patients to the study. Therefore, with around 150 recruiting centres from our pre-existing research network, we would expect to meet the sample size required.

Missing values are to be expected in a study of this kind and will potentially affect certain centres more than others. To allow for potential imputation without introducing significant bias, we will include patients with ≥70% completeness. Multiple imputation methods will be used for the remaining missing data.

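### The primary outcome is called 30-day mortality, but the follow-up rule stops at discharge, so it observes in-hospital mortality up to day 30

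*Protocol article*

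**What the plan says.** The Aims section sets the target: "The primary aim of this study is to describe global 30-day postoperative mortality rates for patients undergoing a trauma laparotomy". Statistical analysis groups centres by the HDI rank of their country, "with 30-day mortality then reported for each HDI group". It justifies 552 patients by 30-day rates of about 9% in high-income countries (HIC) and about 17% in low- and middle-income countries (LMIC). The Discussion again promises 30-day mortality.

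The observation rule is different. Under Study design, enrolment is described "with patients followed until discharge, death or 30 days postoperatively, whichever comes first". The Abstract gives the same rule, and the strengths and limitations box describes a snapshot that runs from injury to discharge. Data collection adds two restrictions: "Data will be collected through access to patient records only at each centre", and "The patient will not be contacted directly in any capacity during their inpatient stay or after the study".

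**The concern.** The label and the follow-up rule define two different outcomes. A patient who leaves hospital on day 6 and dies elsewhere on day 15 is a 30-day death. Under the stated rule, observation of that patient ended on day 6.

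What is at stake is the meaning of the headline result. Two settings with the same true 30-day mortality could show different recorded rates only because one discharges patients earlier, or because more of its patients die after leaving. The HDI comparison would then partly reflect discharge practice. Readers who compare the result with studies that did ascertain deaths to day 30 would also be comparing unlike quantities. The limitations text in the Discussion covers deaths before hospital, before theatre, or without surgery. It says nothing about deaths after discharge.

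**Working it through.** **Step 1. Does any part of the article restore day-30 ascertainment?**

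- Study design speaks of the last patients, "with final 30-day follow-up for the final patients expected to be completed on 30 January 2025". That date is the outer limit of observation. It does not override the discharge rule in the same section.
- Data collection gives each centre's own records as the only source and rules out contact. The independent validator checks case ascertainment and the date and nature of the operation, not vital status.
- Multiple imputation is planned for missing values. If day-30 status were treated as missing after discharge, the stated follow-up would supply no observed post-discharge outcomes from which to impute it.

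No passage describes finding out vital status after discharge.

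**Step 2. Reproduce the stated sample size.** Inputs from Statistical analysis: p1 = 0.09, p2 = 0.17, alpha 0.05, power 80%. Assumed, because not stated: two-sided test and 1:1 allocation.

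n per group = [1.960·√(2·p̄·(1−p̄)) + 0.842·√(p1(1−p1) + p2(1−p2))]² / (p2−p1)², with p̄ = 0.13

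= [1.960·√0.2262 + 0.842·√0.2230]² / 0.0064 ≈ 1.768 / 0.0064 ≈ 276.2, rounded up to 277, or 554 in total.

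This is within 2 of the stated 552, and power at 276 per group is 80.0%. The arithmetic is sound for true 30-day rates.

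**Step 3. What the rule records.** Let s be the share of 30-day deaths that occur after discharge.

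Recorded rate = true 30-day rate × (1 − s)

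Since s cannot be negative, the recorded rate is at most the true rate. The article gives no length of stay and no post-discharge mortality, so every value of s below is an assumption. Power uses the same pooled two-sided formula with 276 per group. The last column is the total needed for 80% power.

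| s in HIC / LMIC | Recorded rates | Difference (points) | Power | Total N |
|---|---|---|---|---|
| 0 / 0 | 9.0% / 17.0% | 8.0 | 80% | 554 |
| 10% / 10% | 8.1% / 15.3% | 7.2 | 75% | 624 |
| 5% / 20% | 8.55% / 13.6% | 5.05 | 47% | 1212 |
| 20% / 5% | 7.2% / 16.15% | 8.95 | 91% | 402 |

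For example, in the third row 0.09 × 0.95 = 0.0855 and 0.17 × 0.80 = 0.136.

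**Step 4. No true difference.** If both settings had 13% true 30-day mortality and s were 5% and 20%, the recorded rates would be 0.13 × 0.95 = 12.35% and 0.13 × 0.80 = 10.4%. That is a gap of 1.95 points produced by discharge alone.

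**The case against.** The strongest defence is that follow-up from records without contact is a deliberate, pragmatic choice for a global snapshot, and that the discharge rule is disclosed in both the Abstract and the Methods. That stands as a defence of the design. It does not make the recorded quantity 30-day mortality.

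The illustration in the table also has limits, and these stand:
- The shares are assumed, and the reverse split raises power.
- The 9% and 17% are taken as complete 30-day ascertainment because the article labels them so. How the cited studies ascertained deaths cannot be seen.
- The primary aim is descriptive, the article itself says an accurate sample size calculation is not feasible, and the equal split is inferred. With 150 centres at 3 to 5 patients each, 450 to 750 patients are expected, so 552 is not a fixed final size.

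Three stronger readings are tempting and are not supported:
- A reader might infer that every post-discharge death is coded as a survivor and that 30-day mortality cannot be obtained at all. The outcome fields are in the online supplement and the analysis plan is not shown, so the coding of discharged patients is unknown.
- A reader might infer that a transfer out counts as a discharge and that the patient is then lost through the exclusion at the receiving centre. The article does not define discharge. The exclusion of transfers for further surgery also does not remove the patient from the centre that did the first laparotomy, if that centre takes part.
- A reader might expect a competing-risk analysis to solve the problem. If every patient is observed to death, discharge or day 30, the cumulative incidence of in-hospital death at day 30 equals the simple proportion. It would still depend on discharge practice.

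**Conclusion.** The point holds as a mismatch between the primary outcome's name and the follow-up rule, together with an omitted limitation. The rule is stated in both Abstract and Methods, so it is not a slip in one place, and nothing else in the article repairs it. The stated rule observes in-hospital mortality up to 30 days after laparotomy, which is a lower limit for 30-day mortality.

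That the HDI comparison depends on discharge timing follows from the rule. The amount does not. Under the assumed shares, power runs from 47% to 91% and the recorded difference from about 5 to about 9 points, against a planned 8. If nearly all 30-day deaths occur before discharge, the effect is small. The documents therefore do not support a claim that the HDI difference is biased in a particular direction, or that power is lost.

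**What to change.** Rename the primary outcome throughout (Abstract, Aims, Statistical analysis, Discussion) as in-hospital mortality up to 30 days after laparotomy. Note beside the sample size that the planning rates are described as 30-day rates.

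If the 30-day label is to be kept, record status at day 30 from the same hospital record as dead, known alive, or unknown after discharge. Report 30-day mortality as a sensitivity analysis with bounds: with D known deaths, U unknowns and N patients, from D/N to (D+U)/N. If many patients are unknown these bounds will be wide, and that should be shown.

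In either case, report length of stay and discharge destination, including transfer out, by HDI group, and state the limitation wherever HDI groups are compared. Some of these fields may already be in the supplementary data set, which is not shown.

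The cost is a less favourable headline label and at most one extra field taken from the record. No patient contact is needed.

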### Patient criteria

We will include patients of all ages who present to hospital with a blunt or penetrating injury and undergo a trauma laparotomy within 5 days of presentation to the treating centre (day 0 being time of presentation). A patient will be included for final analysis if >70% of the data points required have been recorded.

Exclusion criteria are as follows:

Patients undergoing a laparotomy ≥5 days (ie, 120 hours) since presentation to the treating centre.Any relook laparotomy, including transfers from another centre for further and/or definitive surgery.Any laparoscopic (including laparoscopic converted to open), robotic, or image-guided procedures.Patients who have been recently discharged from any hospital (including for non-trauma-related admissions) and have represented within 30 days of discharge.

### Data collection

We aim to collect system, patient, process and outcome data. A data set will be collected on all patients undergoing a trauma laparotomy within the inclusion period (see online supplemental table 1). The included data fields were based on work by similar studies and refined through iterative consultation with a global interdisciplinary consortium of clinicians involved in trauma care.

Data will be collected through access to patient records only at each centre, performed by members of the local study team. The patient will not be contacted directly in any capacity during their inpatient stay or after the study and no direct involvement in patient care will occur. Data will be collected directly onto a well-established secure web-based system, REDCap cloud (or recorded temporarily onto a hard copy data collection form and uploaded to REDCap at a later date).

A local data validator (independent of the local study team) will be appointed at select participating centres to assess the data accuracy and ascertainment. They will independently assess case ascertainment and collect data on two variables, namely the date and nature of the operation. Each centre’s local lead will also be asked to complete a centre survey, to provide more background on their specific hospital settings, infrastructure and capacity. A pilot study was run prior to the main data collection period at multiple centres globally to ensure feasibility in the methodology across multiple settings.

The data collected will include a pragmatic set of variables that allow the proposed research to be conducted, but minimise both risk of identification and exclude extraneous possibly sensitive medical information. Local requisite ethics and approvals will be applied for and be in place before any data collection occurs. The patient consent procedure will depend on the local and national guidance for the collaborating hospitals; specific guidance will be provided to collaborators on consenting if necessary and, where required, written consent forms will be obtained for patient inclusion in the study.

Access to the main data for analysis will be limited to named researchers from the steering committee, however, collaborators at each centre will be able to access their own institutions data during the study period.

### Statistical analysis

A formal statistical analysis plan will be produced. However, in brief, participating centres will be stratified based on their country into groups based on their Human Development Index (HDI) rank, with 30-day mortality then reported for each HDI group. Further analyses will include stratification against other economic and health indices, and multivariable logistic modelling will be used to investigate primary and secondary study aims.

As there are a lack of data on trauma laparotomy globally, performing an accurate sample size calculation is not feasible. Data suggest that 30-day mortality rates following trauma laparotomy in high-income countries (HICs) are around 9%^3^ and in low-income and miffle-income countries (LMICs) are around 17%^17–19^; using an alpha value=0.05 and power=80%, to show a difference between HIC and LMIC settings, a total of 552 patients are required to be recruited to the study. Based on data from other observational studies,^3 7 8^ we would expect over a 30-day observation period each centre to commit around 3–5 patients to the study. Therefore, with around 150 recruiting centres from our pre-existing research network, we would expect to meet the sample size required.

Missing values are to be expected in a study of this kind and will potentially affect certain centres more than others. To allow for potential imputation without introducing significant bias, we will include patients with ≥70% completeness. Multiple imputation methods will be used for the remaining missing data.

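### The 80% power stated for 552 patients assumes independent patients, but the HIC–LMIC comparison is between countries with patients clustered in centres

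*Protocol article*

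**What the plan says.** Under Statistical analysis, the protocol article takes 30-day mortality of about 9% in HIC and 17% in LMIC and concludes: "using an alpha value=0.05 and power=80%, to show a difference between HIC and LMIC settings, a total of 552 patients are required". The abstract repeats the target: "Our sample size calculation suggests we will need to recruit 552 patients from approximately 150 recruiting centres". On recruitment, Statistical analysis adds: "we would expect over a 30-day observation period each centre to commit around 3–5 patients to the study", and with around 150 centres it expects to reach the target.

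The same section groups centres by their country's Human Development Index (HDI) rank and reports mortality by group. It announces a formal statistical analysis plan and, in brief, says that "multivariable logistic modelling will be used to investigate primary and secondary study aims". It gives no ICC, design effect, number of countries or HIC:LMIC split. It also says that an accurate sample size calculation is not feasible, for want of global data. Under Aims, the primary aim is to describe global 30-day mortality.

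**The concern.** Income group is set by country. Every patient in a centre, and every centre in a country, falls on the same side of the HIC–LMIC comparison. No within-cluster contrast offsets the correlation, so the full design effect applies to exactly the comparison that the sample size is built on. The article states the cluster figures (3–5 patients, about 150 centres) but uses them only to show that recruitment is feasible.

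What is at stake is how the result is read. If the analysis respects the clustering and finds no clear HIC–LMIC difference, readers will judge that against a stated 80% power that 552 patients do not provide. The precision of mortality rates by country group is affected in the same way.

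**Working it through.** **Inputs from the article (Statistical analysis).** p1 = 0.09, p2 = 0.17, alpha 0.05, power 80%, total 552, 3–5 patients per centre, about 150 centres.

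**Inputs assumed, because the article does not give them.** Two-sided test; 1:1 split; centre ICC 0.01–0.10; country ICC 0.01–0.05; 40 countries; clusters of equal size.

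**Step 1: reproduce 552.** With mean proportion p̄ = 0.13, the usual formula for two independent proportions is

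n per group = [1.960 × √(2p̄(1−p̄)) + 0.842 × √(p1(1−p1) + p2(1−p2))]² / (p2−p1)²

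= [1.960 × 0.4756 + 0.842 × 0.4722]² / 0.0064 = (0.9322 + 0.3974)² / 0.0064 = 276.2.

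Twice this is 552. Power at 276 per group is 79.97%. Other common versions do not give exactly 552: unpooled 548, arcsine 544, continuity-corrected 602, one-sided 436. The stated total is therefore the independent-patient figure, with nothing in reserve.

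**Step 2: add clustering.** The design effect is DE = 1 + (m − 1) × ICC, and power is recomputed at 276/DE patients per group. The two levels are taken one at a time.

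Centre level, m = 552/150 = 3.68:

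| Centre ICC | DE | Effective n per group | Power at 552 |
|---|---|---|---|
| 0.01 | 1.03 | 269 | 79% |
| 0.02 | 1.05 | 262 | 78% |
| 0.05 | 1.13 | 243 | 75% |
| 0.10 | 1.27 | 218 | 70% |

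Country level, m = 552/40 = 13.8:

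| Country ICC | DE | Effective n per group | Power at 552 |
|---|---|---|---|
| 0.01 | 1.13 | 245 | 75% |
| 0.02 | 1.26 | 220 | 70% |
| 0.05 | 1.64 | 168 | 59% |

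The country figures depend on the assumed number of countries. At country ICC 0.02, 20 countries give 62%, 30 give 67% and 50 give 72%.

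**Step 3: allow for the expected yield.** 150 centres × 3–5 patients = 450–750 patients. Power with equal groups and centre-level clustering only:

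| Patients per centre | Total | No clustering | ICC 0.01 | ICC 0.02 | ICC 0.05 | ICC 0.10 |
|---|---|---|---|---|---|---|
| 3 | 450 | 71.5% | 71% | 70% | 67% | 64% |
| 4 | 600 | 83% | 82% | 81% | 78% | 73% |
| 5 | 750 | 90% | 89% | 88% | 85% | 79% |

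**Step 4: the unstated split.** Without clustering, 552 patients divided 2:1 LMIC:HIC give 73.4%, and 1:2 give 77.0%. The 80% therefore also depends on equal groups.

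**The case against.** Five points can be made for the plan.

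- **The arithmetic is right.** 552 does reproduce. What is missing is an allowance for clustering. This stands: the point concerns an assumption, not a miscalculation.
- **The article qualifies its own figure, and the primary aim is descriptive.** Both are true and both lower the severity. But the caveat cites lack of data, not clustering, and the HIC–LMIC comparison is the only justification given for 552.
- **552 is not a cap.** A reader might infer that the study cannot reach 80% power. The documents do not support that: at 750 patients, power is 80% or more up to a centre ICC of about 0.09, and at 600 up to about 0.03. Such a surplus is a hope about recruitment rather than a planned allowance, and at the low end of the range power is short before any clustering.
- **Variation between income groups is the effect under test.** Only residual correlation within each income group inflates the variance. This stands. The Introduction even reports similar outcomes across major trauma centres in one high-income setting, which hints at a small residual ICC there, though it says nothing about LMICs. The size of the loss is therefore uncertain.
- **The model is left to the analysis plan.** A reader might infer from "multivariable logistic modelling will be used to investigate primary and secondary study aims" that clustering will be ignored, so that confidence intervals are too narrow and the type I error exceeds 5%. The article does not support this. It gives the model in brief and defers to a formal statistical analysis plan that is not shown, and a logistic model may well carry random effects or a cluster-robust variance. Silence on this in a condensed article is not an error.

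**Conclusion.** The concern holds for the sample size statement alone. The 80% attached to 552 patients rests on independence, which the design does not meet, and on an unstated 1:1 split. The direction is certain for any positive residual ICC; the size is not, because the article gives neither an ICC nor a number of countries.

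The loss from centre clustering is modest: about 1 point at ICC 0.01, 5 at 0.05 and 10 at 0.10. It is larger only if mortality also clusters by country within income group, and the 75% to 59% range there rests on an assumed 40 countries of equal size. Within the expected 450–750 patients, the number recruited affects power at least as much as a centre ICC in this range.

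Severity is moderate.

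**What to change.** - State under Statistical analysis that 552 assumes independent patients, a two-sided test and a 1:1 HIC:LMIC split.
- Replace the flat 80% with a short table of power under an explicit design effect, over a stated ICC range at centre and country level and over the expected 450–750 patients. Give the assumed number of countries.
- When the statistical analysis plan is written, confirm that the HIC–LMIC or HDI-group comparison and its confidence intervals account for clustering by centre and country, by random intercepts or a cluster-robust variance.

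The cost is a few sentences and a less favourable stated power. The change requires no more patients and no change to data collection.

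### About 150 centres at 3–5 patients each yield 450–750, so reaching 552 is not assured across the protocol's own range, and 552 is stated as recruited when it is the number that must be analysed

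*Protocol article*

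**What the plan says.** The Statistical analysis section of the protocol article takes 30-day mortality of about 9% in high-income countries (HIC) and about 17% in low- and middle-income countries (LMIC). It arrives at 552 patients "using an alpha value=0.05 and power=80%, to show a difference between HIC and LMIC settings", and describes these as patients to be recruited. On yield it says "we would expect over a 30-day observation period each centre to commit around 3–5 patients to the study", and it concludes "Therefore, with around 150 recruiting centres from our pre-existing research network, we would expect to meet the sample size required". The Methods paragraph of the Abstract pairs the same two figures: "we will need to recruit 552 patients from approximately 150 recruiting centres".

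Three other places bear on this:

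- **Study design** gives each centre one consecutive 30-day period, admits centres with a single case, and plans snowballing to add centres.
- **Patient criteria** keeps a patient in the final analysis only if more than 70% of the required data points are recorded. Statistical analysis puts the threshold at 70% or more and applies multiple imputation to what is still missing.
- **Discussion** suspects that the amount of missing data may be relatively high.

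**The concern.** There are two separate difficulties.

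First, the conclusion that the target should be met is drawn from a range of yields that is never multiplied out. Part of that range falls short of 552, and a reader of the article cannot see this.

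Second, a number derived from a power formula is a number of patients contributing to the comparison. The protocol attaches it to recruitment and then applies a rule that removes patients after recruitment. Multiple imputation fills gaps in the records that are kept; it does not bring back records that fail the threshold. Any such loss takes the analysed number below 552.

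At stake are the stated size and the stated 80% power for the HIC–LMIC contrast, and the precision of the mortality estimates.

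**Working it through.** **Inputs, all from Statistical analysis:** p1 = 0.09 (HIC), p2 = 0.17 (LMIC), alpha 0.05, power 80%, total 552, around 150 centres, around 3–5 patients per centre. Sidedness and the HIC:LMIC split are not stated. I assume two-sided and 1:1 because that combination reproduces 552.

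**1. Reproducing 552.** Pooled normal approximation, no continuity correction, mean proportion p = 0.13:

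n per group = [1.960 × √(2 × 0.13 × 0.87) + 0.842 × √(0.09 × 0.91 + 0.17 × 0.83)]² / 0.08² = 276.2

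Rounded up this is 277 per group, 554 in total; rounded down it is 276 per group, 552. The unpooled formula gives 548 and the arcsine formula 544. One-sided tests (436, or 484 with continuity correction) and the two-sided continuity-corrected test (602) do not reproduce 552. The target stands, and it contains no allowance for losses. Power at 552, all analysed, is 79.97%.

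**2. Recruitment yield.** Yield = centres × patients per centre.

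| Average per centre | Yield from 150 centres | Against 552 |
|---|---|---|
| 3 | 450 | 102 short (18.5%) |
| 3.5 | 525 | 27 short |
| 3.68 | 552 | break-even (552/150) |
| 4 | 600 | 48 over |
| 5 | 750 | 198 over |

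**3. Power over the yield range.** Under 1:1, two-sided 0.05, no clustering and no losses:

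- 450: 71.5%
- 600: 83.2%
- 750: 90.4%

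The split matters. With 30:70 HIC:LMIC, power is about 61% at 450 and 84% at 750. With 70:30 it is about 67% and 86%.

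**4. Removal for incompleteness.** The largest loss that still leaves 552 is 1 − 552/yield:

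- 3 per centre: none, since the yield is already short
- 4 per centre: 1 − 552/600 = 8.0%
- 5 per centre: 1 − 552/750 = 26.4%

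The documents give no loss rate, so the following is an assumed range. Required recruitment = 552/(1 − loss), rounded up:

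| Assumed loss | Recruited for 552 analysed | Per centre at 150 centres |
|---|---|---|
| 5% | 582 | 3.88 |
| 10% | 614 | 4.09 |
| 20% | 690 | 4.60 |
| 30% | 789 | 5.26 |

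At an assumed 30% loss, the required average lies above the top of the protocol's range.

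**The case against.** The case for leaving the text alone has real substance. The protocol says that it would expect to meet the target, and both 3–5 and 150 are approximate. The midpoint gives 600, and break-even sits below the middle of the range. The 3–5 could also describe how individual centres vary around a mean near 4, rather than bounds on that mean. The same paragraph says that an accurate calculation is not feasible. The 150 is not a cap, since snowballing is planned and any hospital performing emergency trauma surgery may join. The primary aim is to describe mortality, so a shortfall would widen intervals and lower power for one contrast without invalidating the main result.

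All of this stands, and it rules out several stronger readings that a reader might infer:

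- **That the study will miss its target.** The documents show only that the lower part of the range does.
- **That the target or the power is presented as secured.** The wording is hedged.
- **That some particular share of patients, such as 10%, will be lost.** No rate is given, and many missing values need not mean many patients under the threshold.
- **That 150 centres must be replaced by 184 (552/3).** This treats 3 per centre as the planning value and is a call to enrol more, which the finding does not need.

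What the objection does not answer is that the conclusion is drawn from 150 centres in the existing network, without snowballing, and does not follow over the whole stated range. Nor does it explain why a number needed for analysis is labelled as the number recruited. The admitted uncertainty about the mortality inputs is a reason to show the range.

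**Conclusion.** The point holds in a limited form. The figure of 552 reproduces and is not in error. The expectation of meeting it is supported at the midpoint of the protocol's inputs but not at an average below 3.68 per centre; at 3 per centre, 450 patients give about 71% power instead of 80%.

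Separately, 552 gives 79.97% power only if every patient is analysed, so calling it a recruitment number is wrong once the completeness rule removes anyone. At 4 per centre the margin is 8.0%.

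The yield arithmetic uses only the protocol's figures. The power figures rest on equal HIC and LMIC groups, a two-sided 0.05 test, no clustering by centre and no losses. An unequal split would lower them. The loss scenarios are assumptions. Severity is minor to moderate, given the descriptive primary aim.

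**What to change.** In Statistical analysis, and in the matching sentence of the Abstract:

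1. Define 552 as analysable patients, after the completeness rule, and settle whether that rule means above 70% or at least 70%.
2. Replace the concluding sentence with the expected yield: about 150 centres are expected to recruit 450–750 patients; 552 requires an average of about 3.7 per centre before losses, or additional centres through the planned snowballing.
3. Report power as about 71% at 450 and 90% at 750, labelled as assuming equal HIC and LMIC groups, a two-sided 0.05 test, no clustering and no losses, and as lower with an unequal split.
4. If a completeness loss is assumed, state it as an assumption and give a range, for example 5–30%, with 582–789 to be recruited.

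The cost is a few sentences and a slightly less favourable stated figure. Eligibility, data collection and the planned number of centres need not change.
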